### Participant timeline {13}

The timeline for participant was detailed in Table 1.

### Sample size {14}

Based on the bladder function recovery rate at 2 weeks post-surgery (Bladder Function Recovery Grade II or higher) observed in pretest, the sample size was determined. The recovery rate for the IC group was 78.95%, compared to 38.89% IDUCs group. Using a unilateral *α* of 0.025, a desired power of 0.9 (i.e., 1 − *β* = 0.9) and the margin of 5%, the sample size was calculated using the following formula.$$n=\frac{{2\overline{p }\overline{q }\left({z}_{\alpha }+{z}_{\beta }\right)}^{2}}{{\left({p}_{1}-{p}_{2}\right)}^{2}}$$

Based on these parameters, the calculated sample size for each group was determined to be 35 cases. To facilitate 1:1 randomization, a total of 70 cases would be required. However, anticipating potential loss due to follow-up dropouts and refusal of participation (estimated at 10–15%), the final minimum number of research subjects for each group was determined to be 39 cases. Therefore, at least 78 participants are deemed necessary to ensure sufficient statistical power for this study.

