### Trial design {8}

This study is a parallel-group superiority randomized controlled trail conducted at a single center, with an allocation ratio of 1:1. We hypothesize that early urinary catheter removal combined with IC is superior in terms of efficiency and effectiveness compared to IDUCs. All participants in the study will be assessed weekly and followed for 3 months. The flow chart is shown detailing the study design, and all interventions and outcome measures are presented in Fig. 1 and Table 1 respectively. This trial follows the report standard of SPIRIT 2013.

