## Statistical methods

### Statistical methods for primary and secondary outcomes {20a}

An intention-to-treat analysis will be performed, utilizing the last available measurement for instance of data lost. The collected data was analyzed using SPSS 20.0 software. Continuity data will undergo normality testing; those with a normal distribution will be analyzed using an independent sample *t* test, while those with a skewed distribution will be assessed using non-parametric test. Chi-square test was used for enumeration data, mean value ± standard deviation ( $$\overline{x }$$±S) for measurement data. When *p* < 0.05, the difference can be considered statistically significant.

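### The printed sample-size formula gives 32 per arm, not the stated 35, and the 5% planning margin is in neither that formula, the stated hypothesis nor the chi-square analysis

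*Protocol article*

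**What the plan says.** All places are in the protocol article.

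- **Sample size {14}, inputs.** The rates come from a pretest: "The recovery rate for the IC group was 78.95%, compared to 38.89% IDUCs group". The section sets a unilateral alpha "of 0.025, a desired power of 0.9", and then adds "the margin of 5%, the sample size was calculated using the following formula".
- **Sample size {14}, formula.** The printed formula is n = 2·p̄·q̄·(z_α + z_β)² / (p₁ − p₂)². It uses a pooled variance and contains no margin.
- **Sample size {14}, result.** From these inputs, "the calculated sample size for each group was determined to be 35 cases". This is raised to 39 per arm for expected losses.
- **Trial design {8}.** "This study is a parallel-group superiority randomized controlled trail conducted at a single center", "with an allocation ratio of 1:1". The hypothesis is that the intervention is superior, and no margin is attached.
- **Statistical methods {20a}.** "Chi-square test was used for enumeration data", with significance at p < 0.05. No margin appears, and the section does not say whether the test is continuity-corrected.

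**The concern.** Two things do not fit together.

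First, the section prints its inputs, its formula and its answer, and the answer does not follow. A reader who repeats the calculation gets a different number and cannot tell which method was used.

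Second, a margin of 5 points is declared as a planning input. That implies a null hypothesis of a difference of at most 5 points. The analysis section names a test of zero difference. If the margin drove the sample size, the planning hypothesis and the analysed hypothesis differ.

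Two readings of success then stay open in one document: a difference shown to exceed zero, or a difference shown to exceed 5 points. Some results would meet the first and not the second. Which one counts should be settled before the data are seen.

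**Working it through.** **Inputs, from Sample size {14}.** p₁ = 0.7895, p₂ = 0.3889, difference 0.4006, p̄ = 0.5892, q̄ = 0.4108. One-sided alpha 0.025 (z = 1.960) and power 0.90 (z = 1.282), so (z_α + z_β)² = 10.507. Margin 0.05, so the difference less the margin is 0.3506. Pooled variance term: 2·p̄·q̄ = 0.4841. Unpooled: p₁q₁ + p₂q₂ = 0.4038.

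**Step 1. The formula as printed.** 0.4841 × 10.507 / 0.4006² = 5.087 / 0.1605 = 31.7, so **32 per arm**. The stated 35 is not reproduced, and a gap of 3 is more than rounding.

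**Step 2. The printed formula with the listed margin.** 0.4841 × 10.507 / 0.3506² = 5.087 / 0.1229 = 41.4, so **42 per arm**.

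**Step 3. Formulas that are not printed.**

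| Formula | Margin | n per arm |
|---|---|---|
| Unpooled variance | 5 points | 0.4038 × 10.507 / 0.1229 = 34.5, so 35 |
| Fleiss (pooled under the null, unpooled under the alternative) | none | 29.6, so 30 |
| Fleiss with continuity correction | none | 34.4, so 35 |
| Farrington–Manning score test | 5 points | 38.5, so 39 |

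Two unprinted routes give 35. One uses the margin and the other does not. The first uses every listed input and is the likelier source, but the article does not settle it.

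**Step 4. Power at 35 analysed per arm.** These figures sum binomial probabilities over all possible tables at the planning rates.

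| Test | Null hypothesis | Exact power |
|---|---|---|
| Chi-square, uncorrected, p < 0.05 | difference = 0 | 93.9% |
| Chi-square, continuity-corrected, p < 0.05 | difference = 0 | 90.6% |
| Wald, lower 95% limit above 5 points | difference ≤ 5 points | 88.7% (90.4% by normal approximation) |

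**Step 5. How often the two criteria disagree.** At 35 per arm and the planning rates, the chi-square succeeds while the Wald limit fails to clear 5 points with probability 5.2% (uncorrected) or 1.9% (corrected). The reverse does not occur.

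**Example.** Take 23/35 against 14/35, a difference of 25.7 points with standard error 11.5 points. The lower 95% limit is 25.7 − 1.96 × 11.53 = +3.1 points. The uncorrected chi-square is 4.64 (p = 0.031), so the test succeeds and the margin is not cleared. With continuity correction it is 3.67 (p = 0.055), both criteria fail, and this example shows no conflict.

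**The case against.** The strongest reply is that this is a transcription fault. Unpooled variance with the margin uses every listed input and returns 35, so the calculation may be sound and the wrong formula printed. That is plausible and limits the severity. It does not remove the second problem, because on that account the margin did drive the sample size and is missing from the hypothesis and the test.

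A reader might infer that the stated 90% power belongs to no planned test. The document does not support that. The planned chi-square reaches at least 90% at 35 per arm in either form, and the corrected form (90.6%) nearly matches the target.

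A reader might also infer that the success criterion is undefined. That too goes further than the text. Trial design {8} says superiority, and Statistical methods {20a} fixes a chi-square at p < 0.05, which in the favourable direction matches a one-sided 0.025. Planning with a margin and then testing zero difference is conservative for that test and does not inflate its type I error.

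Finally, 39 per arm are to be enrolled under intention-to-treat. If all 39 are analysed, exact power is 96.3% (uncorrected), 93.8% (corrected) and 91.1% (Wald against the margin). This stands, and it confirms that the number of patients is not the issue. It depends on no loss to analysis, whereas 35 is the number the section sets as required.

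**Conclusion.** The point holds as an inconsistency of moderate severity. The printed formula gives 32 per arm, or 42 with the listed margin, and never 35. The 5-point margin is absent from the formula, the hypothesis and the test, so the hypotheses at planning and at analysis differ as written.

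The practical size is small. The two criteria would disagree in about 5% of trials (uncorrected) or 2% (corrected), and the margin test would fall 1.3 points short of 90% power at 35 per arm.

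Nothing here shows that the trial is underpowered for its planned test. These figures assume the pretest rates are the true rates and that 35 per arm are analysed. The 88.7% and the disagreement rates also assume a Wald interval, since the article names no margin test.

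**What to change.** Print the formula that produced 35 in Sample size {14}, and carry one hypothesis through the design, sample-size and analysis sections.

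- **Preferred.** Delete the 5% margin and keep the chi-square against zero difference. State whether it is continuity-corrected. Restate the power at 35 analysed per arm as about 94% (uncorrected) or 91% (corrected). If the pooled formula without a margin is kept in print, give its result as 32 and describe 35 as exceeding it.
- **Alternative.** Keep the margin and state the null hypothesis as a difference of at most 5 points. Require the lower 95% limit of the risk difference to exceed 5 points, print the formula with the margin in it, and restate the power at 35 per arm as about 89%.

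Either choice changes text only and adds no patients. It should be made before data lock, so that the criterion is not chosen with the results in view.

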## Assignment of interventions: allocation

### Sequence generation {16a}

As a prospective randomized controlled design, the intervention group and the control group were designed in a 1:1 ratio. With the rank function of the computer EXCEL table to generate 78 random real numbers, sort and group the random data, and participants are grouped accordingly: individuals assigned odd numbers join the intervention group, while even numbers denote control group membership.

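### Thirty-nine per arm allows for about 10% loss, not the stated 10–15%; at 15% it could leave about 33 of the 35 per arm the plan calls for

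*Protocol article*

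**What the plan says.** All of the following is in the protocol article, under Sample size {14} unless another section is named.

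- Assumed rates, from a pretest: "The recovery rate for the IC group was 78.95%, compared to 38.89% IDUCs group".
- Error rates: "Using a unilateral *α* of 0.025, a desired power of 0.9". A margin of 5% is also named.
- Result before loss: "the calculated sample size for each group was determined to be 35 cases", which makes 70 in total.
- Allowance, for dropout during follow-up and refusal to take part: "estimated at 10–15%), the final minimum number of research subjects for each group was determined to be 39 cases". This makes at least 78 in total, described as giving sufficient power.
- Sequence generation {16a}: the allocation list is made with an instruction to "generate 78 random real numbers", so it has as many entries as the minimum total.
- Statistical methods {20a}: counts are compared by chi-square test at p < 0.05, with no margin mentioned. The analysis is by intention to treat, with the last available measurement carried into gaps. Section {20c} adds mean imputation for missing objective data and a per-protocol analysis.

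**The concern.** An allowance given as a range is normally met at its upper end; otherwise the upper end does no work. Here 39 looks like the lower-end figure presented as cover for the whole range. If so, the stated size does not deliver the stated allowance, and the sentence linking 78 participants to sufficient power needs a qualification. The allocation list offers no visible reserve, since it also stops at 78.

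The allowance also adds together two different things. Loss after randomisation reduces the number who can be evaluated. Refusal to take part, if it comes before consent, uses no randomised place, because Implementation {16c} allocates only after the consent form is signed. A reader therefore cannot tell what loss among randomised patients was planned for.

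**Working it through.** **Inputs** (Sample size {14}): p1 = 0.7895, p2 = 0.3889, one-sided α = 0.025, power 0.90, margin 0.05, 35 per arm before loss, loss 10–15%, 39 per arm after loss.

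**1. Reproducing 35.** With unpooled variance and the margin subtracted,

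n = [p1(1−p1) + p2(1−p2)] × (1.960 + 1.282)² / (p1 − p2 − 0.05)² = 0.4038 × 10.507 / 0.3506² = 34.5, so 35.

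This gives the plan's figure and is used below as the margin reading. The continuity-corrected formula without a margin also gives 35. The printed formula has no margin term and gives 31.7, so 32. That is a separate matter; the loss arithmetic here starts from the plan's own 35.

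**2. Reproducing 39.**

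| Loss d | 35/(1−d) | Needed per arm | Left from 39, 39(1−d) |
|---|---|---|---|
| 10% | 38.9 | 39 | 35.1 |
| 12.5% | 40.0 | 40 | 34.1 |
| 15% | 41.2 | 42 | 33.15 |

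The cruder convention of multiplying by (1+d) agrees at the lower end: 35 × 1.10 = 38.5, so 39. At the upper end it gives 35 × 1.15 = 40.25, so 41. On either convention 39 is the 10% figure. The largest loss at which 39 still leaves 35 is 1 − 35/39 = 10.3%. At 15% the shortfall is 3 per arm (42 − 39), or 6 in total (84 − 78).

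**3. Power if 33 per arm remain.** On the margin reading, power = Φ(0.3506/√(0.4038/n) − 1.960):

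- n = 35: Φ(3.264 − 1.960) = 90.4%
- n = 33: Φ(3.169 − 1.960) = 88.7%

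Exact binomial enumeration at the same rates gives:

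| Test | 35 per arm | 33 per arm |
|---|---|---|
| Wald, 5% margin | 88.7% | 86.1% |
| Chi-square, no margin, uncorrected | 93.9% | 93.9% |
| Fisher, no margin | 90.6% | 90.1% |

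The exact Wald figure is already below 90% at 35, so only 88.7 − 86.1 = 2.6 points of its gap at 33 come from loss. On the like-for-like normal approximation the loss costs 90.4 − 88.7 = 1.7 points.

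**The case against.** A reader might infer that the plan's claim of sufficient power is simply wrong at 15% loss. The document does not support that. The test it names has no margin, and at 33 per arm that test still has 93.9% power (90.1% by Fisher). The shortfall appears only if the 5% margin, named in the sample size section but absent from both the printed formula and the statistical methods, is really part of the test. Nor should the 86.1% from exact Wald be set against 90% as the price of dropout, since the same method gives 88.7% with no shortfall at all.

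Thirty-three per arm is also a worst case, for three reasons:

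- The 10–15% includes refusals, and no split is given. Any refusal before consent leaves the 39 untouched. The word could also cover patients who decline to continue, which the exit criteria list, so it cannot all be assumed to come before randomisation.
- Intention to treat with carried-forward or imputed values would keep some lost patients in the primary analysis.
- The primary outcome is at 2 weeks and follow-up runs to 3 months, so later dropout does not affect it.

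The plan also calls 39 a minimum and says at least 78, and nothing forbids recruiting more, although the list as described stops at 78.

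These points limit the consequence and stand. They do not repair the allowance. The sample size section uses none of them to justify 39; it treats the loss as something that inflation must make good. The planned per-protocol analysis would also lose patients directly.

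**Conclusion.** The point holds as an arithmetic mismatch. From 35 per arm, 39 covers a loss of up to 10.3%, while the text claims 10–15%. Cover at 15% would take 42 per arm.

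The consequence is minor: about two evaluable patients per arm, if the whole 15% falls on randomised patients and none are retained by imputation. On the 5%-margin reading this takes power from 90.4% to about 88.7%, just under the stated 90%. Under the no-margin chi-square test it leaves power above 90%. These figures assume that the pretest rates hold. The trial is not shown to be underpowered; the stated allowance is wrong, and it is easily put right.

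**What to change.** In Sample size {14}:

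1. State that 39 per arm allows for 10% loss after randomisation.
2. Give the power if loss reaches 15% (33 per arm) under the test actually planned. That requires saying whether the 5% margin belongs to the test: about 88.7% by the margin formula (86.1% by exact Wald) if it does; 93.9% by chi-square (90.1% by Fisher) if it does not.
3. Count only loss after randomisation in the allowance. Refusal before consent is already covered by the 40% recruitment fraction under Recruitment {15}.

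This takes two or three sentences and no extra patients. The cost is a slightly less favourable stated figure. Keeping the 15% claim instead would mean 42 per arm and an allocation list of 84.

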### Recruitment {15}

Patient recruitment for the study will follow a consecutive enrollment strategy at the First Affiliated Hospital of Army Medical University. Recruitment was initiated in September 26th 2022. Due to the COVID-19, it is expected to be finished by the end of 2024. Participants were recruited by two strategies. Patients from outpatient and inpatient, meeting inclusion criteria, were referred to project researchers for recruitment. Eligible hospitalized patients were recruited. The estimated recruitment fraction is 40%. Seven patients will be recruited per month, and 2–3 of them will be enrolled in this trial.

## Assignment of interventions: allocation

### Sequence generation {16a}

As a prospective randomized controlled design, the intervention group and the control group were designed in a 1:1 ratio. With the rank function of the computer EXCEL table to generate 78 random real numbers, sort and group the random data, and participants are grouped accordingly: individuals assigned odd numbers join the intervention group, while even numbers denote control group membership.

### Concealment mechanism {16b}

The random assignment sequences are generated and managed by an individual not involved in clinical duties ensuring that the allocation remains concealed. This is achieved through the use of sequentially numbered and sealed opaque envelopes, which are then distributed randomly to participants.

### Implementation {16c}

Upon signing the consent form, participants are allocated to either the intervention or control group according to numbers in the envelope.

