## Methods: participants, interventions, and outcomes

### Study setting {9}

All participants are recruited from the First Affiliated Hospital of Army Medical University of PLA in Chongqing, China. The Ethics Committee of this hospital has approved this study protocol, (Approval No.(A)KY2021113)). All potential participants will sign a written informed consent form before allocation.

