#### Exclusion criteria

→Patients with pre-existing urinary dysfunction diseases, kidney diseases, or serious underlying conditions, such as uncontrolled severe anemia, hypertension, diabetes, and cardiovascular or cerebrovascular complications.→Surgical duration exceeding 4 h, or the blood loss surpassing 1000 mL.→Intraoperative injuries to the ureter, bladder, or bowel; Postoperative complications such as vesicovaginal or urethrovaginal fistulas→Conditions requiring emergency intervention or reoperation within 6 h post-operation→Patients with severe mental illness, or cognitive dysfunction.→

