### Who will take informed consent? {26a}

Patients meeting the above inclusion criteria will be informed about this study after admission. Interested patients will attend an orientation session and be allocated a handbook regarding postoperative bladder management before surgery. Participants, who can review and complete consent independently will then be provided with the informed consent form. Those who agree to participate will sign a written informed consent form prior to enrollment.

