### Intervention description {11a}

Health education (preoperative): Prior to the surgery, patients and their family members will be provided with education on IC. This will include an overview of the principles, methodology, and procedural steps of IC, complemented by instructional videos.Supervision and guidance (postoperative days 1–2): Study team members will provide supervision and guidance to patients regarding pelvic floor muscle training (PFMT). Continued education on IC will be delivered through instructional videos to patients and their families.Catheter removal process (postoperative day 3): Following the prescribed fluid intake plan, IDUCs will be removed according to the physician’s instructions. Patients will be encouraged to urinate spontaneously 2–3 times within 2 h of catheter removal. After the last voiding, RUV will be immediately assessed via ultrasound. If RUV exceeds 100 mL, IC will be initiated. The frequency of IC will be adjusted based on RUV. When the frequency of catheterization decreases to once per day and RUV is less than 100 mL after spontaneous urination, bladder voiding function will be considered to be recovered to level II or higher.Patient ability to perform IC will be evaluated by the pencil and paper test [25]. The total score is 15 points, with a score ≥ 9 points indicating patient can perform IC with assistance from medical staff or family. Those scoring < 9 points will require direct assistance from medical staff.Scheduling of IC: The frequency of IC will be tailored according to RUV measurements: 5–6 times daily for RUVs of 350–500 mL (5 times per day: 7:00, 11:00, 15:00, 19:00, 22:00; 6 times per day: 7:00, 11:00, 15:00, 19:00, 22:00, 1:00); 3–4 times daily for RUVs of 200–350 mL (3 times per day: 7:00, 13:00, 19:00; 4 times per day: 7:00, 13:00, 19:00, 22:00); 1–2 times daily for RUVs of 100–200 mL (once per day at 19:00; twice per day at 7:00 and 19:00). Specific timing for catheterization is outlined.Drinking plan: Total daily fluid intake is set 1500–2000 mL, and not exceed 2500 mL [12, 13]. Drink 400–500 mL of each meal (including intravenous infusion, liquid beverages, milk, soup). Between meals, patients may drink 200–300 mL of fluids every time. Fluids should be avoided from 20:00 to 6:00.Voiding diary for IC: Participants will record intake amounts (including intravenous infusion volume during hospitalization), spontaneous voided volume, urination times, IC interval, catheterized volume, uresiesthesia and symptoms over a continuous 24-h period. Milliliter was used for fluid unit. And fluid volume was determined by professional tools.Bladder training: Exception pelvic floor rehabilitation training, patients undergoing IC will participate in bladder training, which includes scheduled urination, urge suppression, and compensatory voiding maneuvers to enhance urinary behavior.

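### Allocation at consent, apparently before surgery, cannot be squared with exclusions judged during or after surgery and an intention-to-treat analysis; fistula, which has no time limit, is the main bias risk

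*Protocol article*

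**What the plan says.** **Timing of allocation.** Implementation {16c}: "Upon signing the consent form, participants are allocated to either the intervention or control group according to numbers in the envelope". Study setting {9} gives the same order: "All potential participants will sign a written informed consent form before allocation". In the consent section {26a}, patients are approached after admission: "Interested patients will attend an orientation session and be allocated a handbook regarding postoperative bladder management before surgery". The consent form comes next. The intervention description {11a} opens with a preoperative step: "Prior to the surgery, patients and their family members will be provided with education on IC". Section {18a} places baseline assessment before surgery.

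**Exclusions.** The list includes "Surgical duration exceeding 4 h, or the blood loss surpassing 1000 mL" and "Intraoperative injuries to the ureter, bladder, or bowel; Postoperative complications such as vesicovaginal or urethrovaginal fistulas". It also includes conditions needing emergency intervention or reoperation in the first 6 h. The fistula item carries no time limit.

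**Analysis.** Section {20a}: "An intention-to-treat analysis will be performed". Section {20c} repeats intention-to-treat and adds a separate per-protocol analysis. The Discussion says the primary outcome takes in every subject whatever their compliance.

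**Blinding.** Section {17a} says participants and staff are hard to blind; only those assessing outcomes that are not self-reported are kept unaware of the arm.

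**The concern.** A patient who is randomised at consent and then has, say, a 5-hour operation is excluded under one section and analysed under another. The article does not say which rule wins. If the exclusion list wins, the analysed set is no longer the randomised set, and the decision is made by people who can know the arm.

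The fistula item is the serious one. It can be met after the two arms have begun to be managed differently, and it bears on bladder function. Excluding on it would condition the primary comparison on an event after treatment, and would remove a harm from a trial whose primary objective {7} includes safety.

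**Working it through.** **1. When each criterion can be known, against when the arms diverge.** The intervention arm has its catheter removed on postoperative day 3 ({11a}); the control arm on day 7 ({6b}). The primary endpoint is at 2 weeks.

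| Criterion | Earliest it can be known | Before day-3 divergence? |
|---|---|---|
| Duration over 4 h; blood loss over 1000 mL | During surgery | Yes |
| Injury to ureter, bladder or bowel | During surgery | Yes |
| Emergency intervention or reoperation | Up to 6 h after surgery | Yes |
| Fistula | Any time after surgery | Not necessarily |

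None of these can be known at a preoperative consent visit. The inclusion criterion that the laparoscopic operation was performed has the same difficulty.

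**2. Is there a rule for these patients?** The exit criteria cover only unwillingness to continue and the researchers' view that continuing would be detrimental. Section {11b} covers switching and withdrawal. Section {20c} covers non-adherence and missing data. None addresses a randomised patient who later meets an exclusion.

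**3. The plan's own sample size.** Inputs from {14}: 78.95% and 38.89%, one-sided alpha 0.025, power 0.90, margin 5%. A continuity-corrected two-proportion formula gives 35 per group. So does the unpooled formula with the margin subtracted (34.5, rounded up). The printed formula gives 31.7, which is a separate matter. Then 35/0.90 = 38.9, so 39 per group and 78 in total. The 10–15% allowance names only dropout and refusal, and the list in {16a} has exactly 78 numbers, so surgical exclusions have no reserve.

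**4. Size of a possible bias (illustration).** Assume equal true recovery of 38.89% in both arms and 39 per arm. Expected recoveries are 0.3889 × 39 = 15.17. Remove k non-recovered patients from one arm only; the false difference is 15.17/(39 − k) − 0.3889:

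- k = 1: 15.17/38 = 39.9%, difference 1.0 points
- k = 2: 15.17/37 = 41.0%, difference 2.1 points
- k = 3: 15.17/36 = 42.1%, difference 3.2 points
- k = 4: 15.17/35 = 43.3%, difference 4.4 points

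**5. Power.** The article gives no rate for these exclusions. Assume 5–10%, followed by the stated 10–15% loss:

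- 39 × 0.95 × 0.90 = 33.3
- 39 × 0.95 × 0.85 = 31.5
- 39 × 0.90 × 0.90 = 31.6
- 39 × 0.90 × 0.85 = 29.8

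Exact binomial power at the planned rates:

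| Per arm | Chi-square, uncorrected | Fisher |
|---|---|---|
| 33 | 0.94 | 0.90 |
| 30 | 0.90 | 0.85 |

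The chi-square test, which {20a} names, still reaches the planned 0.90 at the worst point of this range. A Wald test against the 5% margin would give 0.85 at 30 per arm, but {20a} names no such test.

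**The case against.** **Removal is not stated.** A reader might infer that the plan drops these patients and so breaks its intention-to-treat comparison. The article does not say that. It calls the criteria exclusions and promises an analysis of all subjects; removal is the natural consequence of the first, not a written rule. What stands is an unreconciled conflict.

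**Preoperative allocation is inferred.** No sentence says that the envelope is opened before surgery, the inclusion criterion is worded as if the operation were already done, and the flowchart and timeline table are not shown. The education step in {11a} sits under the intervention but does not say that controls are left out. Even so, the consent sequence, the preoperative education and the preoperative baseline make allocation before surgery the plain reading.

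**Most criteria cannot result from the allocated catheter strategy.** This stands. Duration and blood loss are numeric thresholds, and every item except fistula arises before day 3. Unblinded staff still leave some room for judgement, but the arm-related argument rests mainly on fistula, for which the article gives neither a frequency nor a direction of bias.

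**Power is not the problem.** This also stands. A reader might conclude that the trial becomes underpowered; the chi-square result at 30 per arm does not support it. Subtracting 10–15% for loss is itself pessimistic, because {20a} and {20c} provide for filling in missing outcome data. A shift of 1 to 4 points is small beside the anticipated 40-point difference, though it would matter more if the true difference were smaller.

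**Recruitment is well advanced.** It began in September 2022 and completion was expected by the end of 2024, so moving randomisation helps only patients still to come.

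**Conclusion.** The concern holds as a conflict between rules. Allocation at consent, exclusions judged during or after surgery, and intention-to-treat analysis of all subjects cannot all be applied, and the article does not say which gives way. As a result, membership of the primary analysis set is unsettled for any randomised patient who later meets an exclusion.

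The bias risk attaches mainly to fistula. Its size is unknown; the illustration of 1.0 to 4.4 points assumes one-sided removal of 1 to 4 non-recovered patients from an arm of 39. The loss of power is modest under an assumed 5–10% exclusion rate. The conclusion rests on reading allocation as preoperative, which is a firm inference but not a quoted statement.

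**What to change.** 1. **Patients already randomised.** Keep everyone allocated in the primary intention-to-treat analysis. Report by arm how many met each exclusion criterion. Use exclusion of those meeting the intraoperative and 6-hour criteria only as a sensitivity analysis.
2. **Patients not yet enrolled.** Take consent before surgery, but open the envelope only after surgery, once the intraoperative and 6-hour criteria have been checked and before the day-3 catheter removal. Give the preoperative education on intermittent catheterization to all consenting patients.
3. **Fistula.** Reconcile this criterion with the intention-to-treat rule, so that an event arising after allocation does not remove a patient from the analysis and is recorded as an adverse event under {22}.

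Items 1 and 3 need wording only and can be settled before the data are locked. Item 2 needs a protocol amendment. Its costs are that controls also receive the education and that the time of allocation differs between earlier and later patients, which should be reported.
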